#### *Exploratory Outcomes:*

Additional exploratory outcomes will include time to first hospitalization and ER visit post-intervention period, prescription adherence rates (defined as percentage of filled prescriptions out of total prescriptions) for all medication as well as guideline-directed medical therapy specifically (for heart failure with reduced ejection fraction this would include ACEi/ARB/ARNI, Beta-blocker, SGLT2 inhibitors, and mineralocorticoid receptor antagonist; for HFpEF this would include SGLT2 inhibitors). In addition to 60-day measurements, we will also collect weight measurements at 30 days and 90 days.

#### *Physical Activity*

- We will evaluate how much physical activity/exercise patients are participating in weekly at baseline, and at 60 days by asking patients to estimate the number of minutes weekly that they are participating in formal exercise or physical activity.

#### *General Health Status:*

- We will evaluate patients' general health status using a single general health status question (would you say that in general your health is excellent, very good, good, fair, or poor) at baseline and post-intervention.

Outcomes determined by review of medical, hospital, and billing records, as well as patient surveys and semi-structured interviews. We will also extract medication at baseline and at 60 days to assess for changes in medical therapy. All patients will be provided a scale and blood pressure cuff for weight and blood pressure measurements, respectively. Patients will be instructed to take weights first thing in the morning (or pick a time-up front for all weight measurements for consistency). All patient-reported measures, including KCCQs and CCS-CA scores will be over the phone or in person per patient preference. Patients will come in for lab work at baseline and at 60 days. For patients who are unable to come with for lab work at 60 days (and within the window of 45-90 days), then we will have public health nurses provide outreach to collect blood work in the home. Patients will receive a text message (if they have a cell phone) or phone call on the landline (if no cell phone) to remind them to complete food diaries, weights, and other patient-reported measures in a timely manner. If patients are unable to come in for baseline lab work prior to intervention period, we will use completed lab work as baseline lab work if within 90 days 90 days of the intervention period. For those that have trouble completing written food diaries, we will collect this information verbally over the phone.

For subsequent planning purposes, we will also track costing data to determine the complete cost of the intervention and estimate total program costs (including all resources, even donated, involved in the implementation of the program, but not including research activities such as blood tests).

Comparator: Those randomized to usual care will not receive any home delivery meals but will receive the recipes of healthy recipes that incorporate traditional local foods and educational booklet. They will also receive a gift bag for agreeing to participate in the study and a \$50 gift card upon completion of the study. Given ethical concerns about those not enrolled to receive the food is medicine intervention, after discussion with our community partners, we will provide 2 meals daily (14 meals weekly) for 4 weeks for all patients randomized to the control group after the study period (and outcome assessment) is complete if patients wish to receive meals and no safety concerns are identified.

Blinding of Intervention: Patients will be informed that they are enrolled in a program to receive medically and culturally tailored meals at home, and thus will not be blinded to their randomization status or participation in this trial. Providers will be not blinded to the intervention. Outcomes will be pulled from the EHR from study members, and those performing the analyses will be blinded to randomization status of the patient.

Enrollment Period: To allow time to coordinate the necessary operational and logistical infrastructure for meal delivery based on patient location/community and delivery mechanism, patients will be

consented and enrolled  $t=-45$  to  $t=-1$  days prior to the start of the intervention period ( $t=0$  for all patients). During this time, baseline assessment with surveys and lab work will take place. All patients will then start the study period (and outcome assessment period) at the same  $t=0$ . Any events that take place in the  $-45$  to  $-1$  days prior to the intervention period will not be included as an outcome. Summary of enrollment, intervention, and outcome assessment timeline is shown below.

[figure not shown]

Intervention Duration: The study team will implement the food intervention for 60 days.

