**Research Plan:** We plan to conduct a randomized, comparative effectiveness design trial, with 1:1 randomization. This will be done at two IHS clinical sites in the Gallup Service Unit at Indian Health Service: Gallup Indian Medical Center (GIMC) and Tohatchi Health Clinic (THC), with the plan to expand to Fort Defiance Medical Center and/or Shiprock Medical Center if we are unable to enroll our target sample size.

**Study Population:** All patients 18 years of age or older, with diagnosis of heart failure based on ICD code I50\* with a hospitalization (any cause) in the last 12 months. Only patients with active prescription through IHS and engaged in care at our centers (clinical visit within last 12 months) will be included. We will exclude patients on hospice care or those residing in an acute care or skilled nursing facility, or any patient currently residing outside of the 50-mile IHS Gallup Service Unit catchment area.

**Subject Recruitment:** Eligible patients are identified through a query through iCARE, a EHR based data system through the IHS EHR. Patients with ICD10 diagnostic criteria for HF will be identified (ICD10\*). The inclusion criteria will be all adults  $\geq 18$  years, who have a prescription in the IHS system in the last 12 months and have had a clinical visit at GIMC or THC in the last 12 months, as well as a hospitalization (all-cause) in the last 12 months. Patients will be consented verbally either at the health center or verbally over the phone to enroll. If we have not met our 50% enrollment goal by 6 months, we will expand enrollment to another Navajo IHS site—Fort Defiance and/or Shiprock Medical Center, and enroll patients with ER visit (rather than just hospitalization) in the last 12 months.

**Enrollment:** All patients that meet eligibility criteria and consent to participate will be enrolled to receive meal delivery simultaneously: all enrolled patients will start receiving the intervention at the same starting time point,  $t=0$ . Patients randomized to usual care will also start the “intervention” of usual care at the time  $t=0$ , so that all patients will have outcome assessment on the same time schedule. For operation and logistical considerations, all baseline assessment (including consent, enrollment, baseline surveys and lab work) will occur in the enrollment period (-45 to 0 days prior to the intervention period). No clinical events will be included during the enrollment period as an outcome.

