## - Phase II: Comparativeness effectiveness trial of Medically and traditionally tailored meals for Heart Failure

We will conduct a comparativeness effectiveness trial to evaluate the impact of providing medically and culturally tailored Indigenous focused meals delivered to heart failure patients. Meals will be prepared, packaged, and delivered once weekly, with delivery mechanism based on community and patient preference. Two meals will be provided daily for 60 days. Along with the meals, patients will also receive recipe cards with each meal, as well as educational information regarding the meals, traditional food items included, and nutritional information, to educate on the health benefits of the food provided, as well some information regarding the traditional foods included and from where they were sourced. Additionally, patients will receive one cooking class conducted by a Diné Registered Dietician ([name]) to learn how to make a few key recipes from the meal plan, all utilizing locally available ingredients.

**Baseline Characteristics:** In addition to the American Heart Association sociodemographic core measures, we will also collect tribal affiliation, language, and in which local chapter/community patients reside.

**Endpoints:** The primary outcome for the trial will be the proportion of patients who have a hospitalization or ER visit for any cause within 90 days post intervention period (all patients will start the study at t=0 as described above). We will not include hospitalizations that occur electively for an elective procedure.

Secondary outcomes will include: heart failure hospitalizations specifically, ER visits for volume overload specifically (ER visits for lower extremity edema, dyspnea, with clinical evaluation consistent with volume overload), change in weight and body mass index at 60 days from baseline, Kansas City

Cardiomyopathy Score (and its components including summary score, physical limitation score, symptom frequency score, quality of life score and social limitation score)[10], and the following lab parameters and biomarkers at baseline and at 60 days: albumin, prealbumin, creatinine, NT-proBNP, HbA1c, Total cholesterol, LDL-C, HDL-C, Triglycerides, CRP, urine albumin:creatinine ratio. Lab work will be permitted to be collected 14 days before 60 days mark and up to 30 days after (from 46 days-90 days post intervention period).

*Additional secondary outcome measures:*

*Diet Quality*

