#### Inclusion/Exclusion Criteria

##### Inclusion

- Age  $\geq 18$  years
- ICD I50\* diagnosis
- Clinical encounter in last 12 months
- Prescription in IHS system in past 12 months
- Primary care physician at one of the two IHS sites
- Hospitalization or ER visit (any cause) in the past 12 months

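### The fallback for missed baseline lab draws is wider than the stated baseline window, gives no direction relative to t=0, and does not exclude samples from acute care

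*Protocol*

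**What the plan says.** Three places in the protocol set the timing of baseline laboratory work.

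- The Enrollment paragraph of the Research Plan: "all baseline assessment (including consent, enrollment, baseline surveys and lab work) will occur in the enrollment period (-45 to 0 days prior".
- The Enrollment Period paragraph gives the window as t=-45 to t=-1 and adds: "During this time, baseline assessment with surveys and lab work will take place".
- The General Health Status section makes an exception. Its condition is "If patients are unable to come in for baseline lab work prior to intervention period", and its rule is "we will use completed lab work as baseline lab work if within 90 days 90 days of the intervention period". The repeated words are a typing slip and not the issue.

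Two other places bear on what the exception lets in. The inclusion list requires "Hospitalization or ER visit (any cause) in the past 12 months"; the Study Population paragraph names hospitalization only. The Statistical Analysis section tests within-group change to week 8 in laboratory values and biomarkers by paired t-test, so the baseline value enters every one of those results directly.

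**The concern.** The exception leaves three things open. It reaches further back than the window set for all baseline labs. It does not say on which side of t=0 the result must fall. It does not say in what setting the blood may have been drawn.

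The setting matters most. Everyone in the trial has been selected for recent acute care, so inpatient or ER results within the look-back are foreseeable for some patients. The laboratory endpoints include NT-proBNP, CRP, creatinine, albumin and prealbumin, which can be displaced during an acute illness. If such a value stands as baseline, its return to the patient's usual level by day 60 is counted as change over the intervention. A within-group test cannot separate that from an effect of the meals, and a recovery in the meal arm could be reported as an improvement.

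**Working it through.** **Windows.** Inputs: baseline window from day -45 (Enrollment and Enrollment Period paragraphs); fallback limit 90 days (General Health Status); 60-day lab window "from 46 days-90 days post intervention period" (Endpoints), restated as "within the window of 45-90 days" (General Health Status); meals for 60 days (Intervention Duration). Days are counted from t=0.

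- Extra look-back under the fallback: 90 - 45 = 45 days, twice the stated window.
- Longest gap from baseline to the 60-day sample under the main rule: 90 + 45 = 135 days.
- The same gap under the fallback, read backwards from t=0: 90 + 90 = 180 days.
- If the 90 days ran in both directions, a baseline could be dated up to day +90. That range would include all 60 days of meals and the whole follow-up window (90 - 46 + 1 = 45 days, or 46 days if it opens on day 45).
- If the 90 days run backwards only, there is no overlap with meals.

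**Effect on the within-group test.** Let p be the share of an arm whose baseline comes from an acute episode, and d the mean amount by which those values sit above the same patients' stable level (negative for markers that fall in acute illness). With no effect of the meals and recovery by the 60-day sample,

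mean change in the arm = -(p × d).

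This is nonzero whenever p and d are nonzero. The paired t-test treats it as change.

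**Effect on a comparison between arms.** The corresponding term is -(p₁d₁ - p₀d₀), with subscripts 1 for meals and 0 for usual care. It is zero in expectation if use of the fallback and the displacement are alike in the two arms. What remains is added variance, because acute and stable baselines are mixed.

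**What can be filled in.** The protocol gives neither p nor d. It does not state how many patients are expected to miss the baseline draw, how often an acute result would then be chosen, or how far any marker moves. No numerical bias follows from it.

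**Primary outcome.** The sample size rests on event proportions of 29% and 13%. With 80% power, alpha 0.05 (two-sided assumed), 1:1 allocation and pooled variance, the two-proportion formula gives 101 per arm, or 202, against the stated 204. No laboratory value enters this calculation or the primary endpoint.

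**The case against.** The fallback is an express exception for patients who cannot attend, and the other two paragraphs give the general rule. A reader might call this a flat contradiction. That is too strong: the conflict is with the unqualified wording of the Enrollment paragraph and its restatement, neither of which mentions an exception. The texts need aligning, but the exception itself is legitimate.

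A reader might also infer that the protocol allows baselines drawn after meals start. The wording does not bar it. But completed lab work that stands in for a missed earlier draw most naturally means an existing earlier result, and the two-sided reading would run through the follow-up window, which is implausible. This is an ambiguity and not a stated rule.

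It might be inferred that fallback values will mostly come from the acute episode. The document does not support that. Eligibility also requires a clinical encounter and a prescription within 12 months, so outpatient results may exist as well, and the qualifying event may lie well outside 90 days.

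A bias between arms might be suspected because patients are not blinded. It would require fallback use to differ by arm, and the protocol does not say when allocation is disclosed relative to the baseline draw. It stays conjecture.

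Finally, choosing among several eligible chart results is detail that a statistical analysis plan may hold, and its absence here is no finding. What stands is that the protocol itself states a rule for accepting baseline results, and that rule, followed as written, admits acute-care samples.

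**Conclusion.** The point holds as a defect in a stated data-collection rule, confined to secondary laboratory outcomes. The window mismatch (45 against 90 days, with the longest interval rising from 135 to 180 days) and the missing direction and setting are plain on the page. The consequence for the within-group tests rests on two assumptions: that some patients use the fallback, and that some of their results come from acute care. The entry criteria make the second foreseeable, but the protocol gives no frequency for either, so no percentage should be attached to the distortion. Comparisons between arms would lose some precision; a systematic bias there is not shown. The primary outcome and the sample size are untouched.

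**What to change.** Reconcile the General Health Status section with the Enrollment and Enrollment Period paragraphs, so that all three give the same baseline window and the first two acknowledge any exception. If the fallback is kept, state that a result used as baseline must be dated before t=0 and drawn outside a hospital admission or ER visit, and that otherwise the baseline laboratory value is treated as missing.

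The cost is a short amendment, a check of date and setting when results are extracted, and a few more missing baseline laboratory values.

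The exclusion should not be extended to 60-day samples. Admission or ER attendance after t=0 is the primary outcome, so dropping follow-up values drawn at such events would condition on a post-randomization outcome. If the meals change admissions, that would produce missingness that differs between the arms.

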#### Inclusion/Exclusion Criteria

##### Inclusion

- Age  $\geq 18$  years
- ICD I50\* diagnosis
- Clinical encounter in last 12 months
- Prescription in IHS system in past 12 months
- Primary care physician at one of the two IHS sites
- Hospitalization or ER visit (any cause) in the past 12 months

##### Exclusion

- Hospice care
- Living in acute rehabilitation or skilled nursing facility
- Living outside the Gallup Service Unit (outside 50-mile catchment area)

How will eligibility be determined, and by whom?

- Eligibility of patients will be assessed by the study team based on the patient's medical record.

**Methods to Reduce Loss to Follow-up:** Patients that do not pick up meals in the planned mechanism within 2 days of planned pick up, will have meals delivered to them at home by a CHR. If patients are not participating in the study as planned, they will be contacted by phone. If unable to reach by phone x 3 attempts, family members will be contacted. If unable to reach anyone, then we will have a public health nurse/community health representative conduct a home visit.

311

312

313

314

315

316

317

318

319

320

321

322

323

324

325

326

327 **Data Collection Timeline**

| Time Period                                     | Baseline                                                                                                                                         | Intervention 30 days | Intervention 60 days | 60 days                                                                                                                                          | 90 days     |
|-------------------------------------------------|--------------------------------------------------------------------------------------------------------------------------------------------------|----------------------|----------------------|--------------------------------------------------------------------------------------------------------------------------------------------------|-------------|
| Patient Surveys/
Patient Related Outcomes    |                                                                                                                                                  |                      |                      |                                                                                                                                                  |             |
|                                                 | X                                                                                                                                                |                      |                      | X                                                                                                                                                |             |
|                                                 | - KCCQ12
- USDA Food insecurity
- DSQ10
- CCS Score
- Nourishment Scale
- Financial Stress Scale
- Exercise
- Health status |                      |                      | - KCCQ12
- USDA Food insecurity
- DSQ10
- CCS Score
- Nourishment Scale
- Financial Stress Scale
- Exercise
- Health status |             |
| Lab work                                        |                                                                                                                                                  |                      |                      |                                                                                                                                                  |             |
|                                                 | X                                                                                                                                                |                      |                      | X                                                                                                                                                |             |
|                                                 | - CMP
- CRP
- HbA1c
- Lipid panel
- Prealbumin                                                                                       |                      |                      | - CMP
- CRP
- HbA1c
- Lipid panel
- Prealbumin                                                                                       |             |
| Clinical measures                               |                                                                                                                                                  |                      |                      |                                                                                                                                                  |             |
|                                                 | X                                                                                                                                                | X                    |                      | X                                                                                                                                                | X           |
|                                                 | Blood Pressure                                                                                                                                   |                      |                      | Blood Pressure                                                                                                                                   |             |
|                                                 | Weight                                                                                                                                           | Weight               |                      | Weight                                                                                                                                           | Weight      |
| Primary Outcome: ER visits and hospitalizations |                                                                                                                                                  |                      |                      |                                                                                                                                                  |             |
|                                                 | X                                                                                                                                                | X                    |                      | X                                                                                                                                                | X (90 days) |
| Food Survey                                     |                                                                                                                                                  |                      |                      |                                                                                                                                                  | X           |

328

329

